## Abstract

**Background:**

For treating deep caries lesions, selective or stepwise (one- and two-step) incomplete excavation seems advantageous compared with complete caries removal. However, current evidence regarding the success, as defined by not requiring any retreatments, or survival of teeth after different excavations is insufficient for definitive recommendation, especially when treating deciduous teeth. Moreover, restoration integrity has not been comparatively analyzed longitudinally, and neither patients’, dentists’ or parents’ preferences nor the clinical long-term costs emanating from both initial and retreatments have been reported yet.

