### Objectives and hypotheses

The study aims at comparing the success (the probability of not requiring any re-interventions) and the survival (the probability of not requiring tooth removal) of selectively excavated versus stepwise excavated vital, non-symptomatic deciduous molars with deep lesions. In addition, we assess the restoration integrity of selectively excavated versus stepwise excavated deciduous molars, evaluate the preference of patients, parents and dentists for one of both strategies, and comparatively assess the costs associated with each strategy.

Our primary hypothesis is that success rates differ significantly between selectively excavated and stepwise excavated teeth. Secondary hypotheses are that restoration integrity is assumed to significantly differ between selectively excavated and stepwise excavated teeth. Moreover, we hypothesize that patients’, parents’ and dentists’ preference is significantly different for selectively excavated versus stepwise excavated teeth. Eventually, both initial and long-term costs of excavation methods are supposed to significantly differ.

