### Allocation and blinding

If more than one primary molar is eligible, the decision as to which tooth will be included into the study will be performed using random number tables (WH) before treatment is commenced. Sequence generation will be performed after inclusion via random number tables (WH). Allocation will be performed via sealed opaque envelopes after the six-monthly recall examination (six months after selective excavation) by the treating dentists. Thus, both the first excavation step and the first re-examination will be performed blinded as to whether further excavation will be performed or not. Clinical follow-up examinations will also be performed blinded to treatment group allocation. Blinding during the second excavation step and blinding of patients as to which treatment was performed will not be possible, but patients will be informed not to reveal treatment allocation to the examiner during follow-up examinations.

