### Outcomes

Outcomes will be assessed by the treating dentists or study nurses. The primary outcome of the study will be success (not requiring any re-intervention). Secondary outcomes will include survival (not requiring extraction), restoration integrity, assessed via modified USPHS-criteria [13], patients’ subjective assessment of the treatment using a visual analogue scale (for stepwise excavation, assessments will be performed twice and mean visual analogue scale results will be calculated), dentists’ and parents’ subjective assessment of the treatment using grades 1 (very good) to 6 (very bad) and initial and follow-up treatment costs (calculated by combining costs for staff, as assessed by time required for the procedures and the number of personnel involved, and costs for transportation of patients or materials).

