**Table 2 Tab2:** **Timing of measurements**

**Measures**	**Preoperative**	**First step**	**After six month/second step**	**Follow-up**	**Retreatment**
Demographics	x				
Dental history	x				
Caries risk	x				
ICDAS score	x				
Sensitivity testing	x	x	x	x	
Radiographic depth	x				
Radiographic endodontic status		(x)	(x)	(x)	(x)
Dental anxiety	x				
Cooperation		x	x		x
Subjective assessments		x	x		x
Costs (time, staff and material)		x	x		x
Clinical outcomes			x	x	x

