### Data analysis and statistical evaluation

The statistical evaluation will be performed using SPSS 20.0. Descriptive statistics will be calculated according to distribution of data. Log rank tests will be used to compare success and survival between groups, with effects of possible confounders (age, gender, dental anxiety, cooperation, use of local anesthetics, caries risk, dental arch, first or second molar, surfaces and center) being assessed. Moreover, we will use two-sided independent t tests or Mann-Whitney U test (to compare visual analogue scale results and costs) as well as chi-square tests (to compare restorative integrity and subjective grading of treatments).

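### Costs are compared with an unadjusted two-sample test although each child's first-session cost, recorded before allocation, could serve as a baseline covariate; the loss is precision only, of unknown size

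*Protocol article*

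**What the plan says.** The section on data analysis and statistical evaluation assigns costs to "two-sided independent t tests or Mann-Whitney U test (to compare visual analogue scale results and costs". Covariates appear in a different sentence of that section, tied to other outcomes: "Log rank tests will be used to compare success and survival between groups, with effects of possible confounders". First-session cost is not on that list.

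The cost outcome is described under Outcomes as "initial and follow-up treatment costs (calculated by combining costs for staff" and further components. The Overview likewise says that initial and follow-up treatments are both costed. The Abstract's background speaks of "the clinical long-term costs emanating from both initial and retreatments", and the hypotheses state that "both initial and long-term costs of excavation methods are supposed to significantly differ". No passage gives a formula for the cost variable that enters the test.

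On timing, the allocation section opens the envelopes after the six-month recall and says that "both the first excavation step and the first re-examination will be performed blinded as to whether further excavation will be performed" or not. In Table 2, the row "Costs (time, staff and material" is marked separately for the first step, the six-month or second step, and retreatment.

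**The concern.** In most trials the cost of initial treatment follows randomization and is part of the treatment effect. Here it does not. The first session is the same procedure in both arms and is finished six months before anyone knows the arm. Its cost will vary between children (chair time, staff, travel, anesthetic, an occasional pulpotomy), but allocation cannot cause that variation. It is a recorded pre-allocation measurement, and probably a predictor of what the same child's later sessions cost.

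An unadjusted two-sample test makes no use of it. If the first session is part of the compared total, its between-child variation adds noise to the arm comparison. If it is not, its predictive value for later costs is ignored. At stake is the precision of a stated secondary hypothesis, which the Discussion also wants to use for cost-effectiveness arguments.

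**Working it through.** **Figure to reproduce.** There is none. The article gives no SD, correlation, effect size or power for costs; its sample size calculation concerns success only. The sizes below therefore rest on assumed ranges.

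**Notation.** Let C1 be first-session cost (before allocation) and C2 all later cost (second session and retreatments), with SDs s1 and s2 and correlation r. Put k = s1/s2. The variance of the arm difference in means is proportional to:

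- unadjusted total C1 + C2: s1² + s2² + 2·r·s1·s2
- total or C2, adjusted for C1 by linear regression: s2²·(1 − r²)
- unadjusted C2 alone: s2²

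**Direction.** The first minus the second is s1² + 2·r·s1·s2 + r²·s2² = (s1 + r·s2)². This is never negative and is zero only if r = −s1/s2. In large samples, then, adjustment cannot lose precision against the unadjusted total, whatever the SDs. Against unadjusted C2 alone, the share of variance removed is r², also never negative.

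**Size for a total, closed form.** Share removed = 1 − (1 − r²)/(k² + 1 + 2·r·k):

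| k (assumed) | r = 0 | r = 0.2 | r = 0.4 |
|---|---|---|---|
| 0.25 | 6% | 17% | 33% |
| 0.5 | 20% | 34% | 49% |
| 1 | 50% | 60% | 70% |

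For example, k = 0.25 and r = 0 gives 1 − 1/1.0625 = 0.06. With k = 1 and r = 0.4 it is 1 − 0.84/2.8 = 0.70. The adjusted standard error is 0.97 and 0.55 times the unadjusted one in these two cases.

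**Size for post-allocation cost only.** The share is r²: 0%, 4% and 16% for r = 0, 0.2 and 0.4.

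**Simulation.** The closed form uses one s2 and one r for both arms, although only stepwise children have a planned second session. A simulation dropped that simplification. Its assumptions were lognormal session costs with mean 1, CV 0.3 or 0.5, correlation parameter 0 or 0.4, a second session of mean cost 1 in the stepwise arm only, and 66, 114 or 150 children per arm, with 800 simulated trials per scenario.

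- Retreatment 20% (selective) against 10% (stepwise), mean cost 1.5. The true difference is 1 − 0.10 × 1.5 = 0.85 session costs. Adjustment removed 20% to 47% of the variance. Power was about 1.00 throughout.
- Retreatment 30% against 10%, mean cost 3. The true difference is 1 − 0.20 × 3 = 0.40. Adjustment removed 4% to 21%. Taking the first-session cost out of the comparison raised power by about 1 to 8 points, for example from 0.52 to 0.60 with 114 per arm, CV 0.5 and correlation 0.4. Power was computed for post-allocation cost rather than for the regression, but the two standard errors nearly coincide (0.190 and 0.189 in that example).

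The mean estimated difference agreed to within 0.01 with and without adjustment in every scenario. In these scenarios the largest variance gains fell where power was already near 1.00.

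**The case against.** The strongest reply is that nothing here is wrong. An unadjusted comparison of a randomized secondary outcome is legitimate, and a condensed article may leave covariates to an analysis plan that is not shown. The first half stands: this is not an error of validity. The second half does not settle the matter, because the article is not silent. It names a specific unadjusted test for costs and attaches its covariates to other outcomes.

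A second reply also stands in part. The compared variable is never defined. The Abstract's background sentence describes what earlier literature lacks, and the hypothesis on initial and long-term costs can be read as two comparisons. If follow-up costs are tested alone, first-session noise is absent and only the gain from correlation remains. The point must therefore be put conditionally.

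Third, the size is assumption throughout. The article does not say whether teeth that needed a pulpotomy at the first step are still allocated, which affects how variable first-session cost is. The variance formulas describe a difference in means and do not carry over directly to the Mann-Whitney option. The article also promises no confidence interval for costs.

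A reader might infer that the cost comparison is biased, or that the trial forgoes a definite number of children's worth of information. The documents support neither: first-session cost is balanced by randomization in expectation, and no cost SD or correlation is given from which such a number could be fixed.

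**Conclusion.** The point holds as one of efficiency. The article fixes an unadjusted test for costs while collecting, before allocation and blind to arm, a baseline cost for every child. The test is unbiased and keeps its type I error. That adjustment does not reduce large-sample precision follows from algebra; how much it helps cannot be read from the documents. For a total including the first session, the assumed ranges give 6% to 70% of the variance in closed form (k from 0.25 to 1, r from 0 to 0.4) and about 4% to 47% in simulation. For post-allocation cost alone the closed form gives 0% to 16%. The test result may be unaffected if the extra session in the stepwise arm dominates the cost difference. The benefit would then lie in a narrower interval for the mean difference, which is the quantity a cost-effectiveness argument needs.

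**What to change.** Define the cost variable explicitly (the period covered, and whether the first session is included). Replace the two-sample test for costs by a linear regression of cost on arm, with the child's own first-session cost and center as covariates and robust or bootstrap standard errors to allow for skewness. Report the adjusted mean difference with its 95% confidence interval, and the unadjusted difference beside it. For the same children, the adjusted estimate is identical whether the outcome is the total or the post-allocation cost, because the covariate absorbs the first session.

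This takes a sentence or two in the analysis section, preferably before outcome data are examined. Table 2 already schedules every input, so no additional patients, visits or measurements are needed.

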**Methods/Design:**

The planned study is a prospective multicenter, two-arm parallel group, randomized controlled clinical trial comparing selective and stepwise excavation in deciduous molars with deep, active caries lesions without pulpal symptoms. We will recruit 300 children aged between three and nine-years-old with a minimum of one such molar. Patients participating in another study, or those with systemic diseases, disabilities or known allergies to used materials as well patients with teeth expected to exfoliate within the next 18 months will be excluded. After inclusion, sequence generation will be performed. Initial treatment will follow dental routine. During excavation, leathery, moist and reasonably soft dentin will be left in proximity to the pulp followed by adhesive restoration of the cavity. Afterwards, patients’, dentists’ and parents’ subjective assessment of the treatment will be recorded using visual analogue or Likert scales. Re-examination will be performed after six months, and only then teeth will be allocated to one of the two interventions. Selectively excavated teeth will not be treated further, whilst for stepwise caries removal, a second excavation will be performed until only hard dentin remains. Clinical re-evaluations will be performed after 12, 24 and 36 months. Restorations will be reassessed using modified Ryge criteria. Objectively or subjectively required retreatments will determine success and survival. Retreatments will be evaluated both subjectively and regarding generated costs.

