### Sample size

The required sample size was calculated based on the primary outcome parameter, success (see below). We anticipate a hazard ratio of 1.3 [21] of stepwise excavated compared with selectively excavated teeth. If α = 0.05 and 1-β = 0.9, a sample size of n = 66 per group is required. Assuming an annual drop-out rate of 20%, 114 patients per group will be required. The total required sample size would thus be n = 228. To allow possible subgroup analyses, a total of 300 patients will be recruited (n = 100 per center).

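### Comparing the ordered 1-to-6 parent and dentist grades with an ordinary chi-square test ignores their order and loses power that a rank test already in the plan would keep

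*Protocol article*

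**What the plan says.** Under Data analysis and statistical evaluation, the protocol article divides the secondary comparisons in two. One group gets "two-sided independent t tests or Mann-Whitney U test (to compare visual analogue scale results and costs"; the other gets "chi-square tests (to compare restorative integrity and subjective grading of treatments". It does not say which chi-square variant is meant and gives no reason for treating the grades differently from the visual analogue scale.

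Under Outcomes, dentists and parents give their "subjective assessment of the treatment using grades 1 (very good) to 6 (very bad"), so the ordering of the grades is explicit. For the restorations, the same section names only "restoration integrity, assessed via modified USPHS-criteria [13"], and the abstract says "Restorations will be reassessed using modified Ryge criteria". Neither place states the number of levels, their order or any dichotomy.

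Both outcomes are secondary: "Secondary outcomes will include survival (not requiring extraction), restoration integrity" and the subjective assessments are listed together. The preference hypothesis under Objectives and hypotheses is non-directional: patients', parents' and dentists' "preference is significantly different for selectively excavated versus stepwise excavated teeth".

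**The concern.** For parents and dentists, the chi-square test on grades is the only comparison the article names. The natural alternative is that one strategy is graded somewhat better throughout. A rank or trend test puts all its sensitivity on that one direction. An ordinary chi-square test would give the same p-value if the six grade labels were shuffled, so it dilutes a consistent shift across five contrasts.

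Two consequences follow. A real difference in parents' or dentists' assessment is easier to miss. And a significant result says only that the distributions differ; it does not itself say which strategy was graded better, which is what a preference question asks.

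**Working it through.** **Inputs from the article.** Six ordered grades (Outcomes); chi-square for grades (Data analysis); 66 and 114 per group and 300 recruited (Sample size). With 1:1 allocation, which is an assumption, 300 gives 150 per group. These sizes were derived for the primary outcome only ("If α = 0.05 and 1-β = 0.9, a sample size of n = 66 per group is required"). The article states no power or effect for the grades, so there is no figure of the plan to reproduce here. The sizes serve only as a realistic range.

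**Assumptions.** Two-sided α = 0.05; a proportional-odds shift between arms; four assumed grade distributions (spread, uniform, skewed, very skewed). None of the shares or odds ratios comes from the article.

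**Step 1: effect of the degrees of freedom.** Suppose a consistent shift produces the same noncentrality λ in both tests. Power is then P(χ²(df, λ) > critical value).
- Rank test, df = 1: 80% power needs λ = 7.85.
- Six-level chi-square, df = 6 − 1 = 5: at λ = 7.85 the power is 55.5%; 80% needs λ = 12.83.
- λ grows in proportion to sample size, so the ratio of sample sizes is 12.83 / 7.85 = 1.63.

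**Step 2: simulation.** There were 20,000 tables per scenario, comparing Pearson chi-square with the tie-corrected Mann-Whitney test. The odds ratio was set so that Mann-Whitney has about 80% power.

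| Per group | Odds ratio (range over four distributions) | Chi-square | Mann-Whitney |
|---|---|---|---|
| 66 | 2.38–2.51 | 53–55% | 80–81% |
| 114 | 1.93–2.02 | 53–56% | 79–81% |
| 150 | 1.77–1.86 | 54–55% | 80% |

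The loss is about 25 points at every size, in agreement with step 1.

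**Step 3: fixed effects, 150 per group.** With odds ratio 1.5, chi-square has 23–29% power and Mann-Whitney 44–52%. With odds ratio 2.0, the figures are 66–75% and 88–92%.

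**Step 4: a different model.** A latent normal scale was cut at assumed shares 30/35/20/10/3/2%, with 120 per arm and 3,000 trials. A shift of 0.4 SD gives 59% against 83%; a shift of 0.3 SD gives 33% against 58%.

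**Step 5: validity.** Both tests hold their type I error. Pearson chi-square becomes conservative, about 3–4%, when the upper grades are sparse.

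**Step 6: restoration integrity, if ordered.** Where a rank test has about 80% power, chi-square has 70–71% with three levels (about 9 points lost) and 64–65% with four (about 16 points lost). With two levels nothing is lost.

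**Step 7: where chi-square wins.** If one arm is more polarised without being better or worse on balance (150 per group), chi-square has 83% power and Mann-Whitney about 5%.

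**The case against.** **The chi-square test is valid and has a use.** The hypothesis is non-directional, and step 7 shows a pattern that only the chi-square test would find. This stands: it would be wrong to say that the planned test has no benefit or that changing it has no downside. But a difference in polarisation on a best-to-worst scale would not show that either strategy is preferred.

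**The variant is not fixed.** The wording does not exclude a linear-by-linear trend chi-square, whose power in the simulations was within about 7 points of Mann-Whitney. This also stands. If that test was meant, naming it settles the point; without the name, most readers will take the ordinary test.

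**Direction can be read from the descriptive statistics.** This is true, and a Mann-Whitney p-value also needs them. The direction argument is therefore secondary to the power argument, though a common odds ratio supplies both direction and size.

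**Stronger readings that the article does not support.** A reader might infer that restoration integrity suffers the same loss. The article gives no levels or ordering for it, and a dichotomised score would lose nothing. A reader might also infer that the whole preference hypothesis rests on chi-square tests. The patients' visual analogue results already have a t test or rank test; only the parent and dentist parts are affected. Sparse cells at the worst grades likewise depend on assumed shares and are not a stated fact.

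**Conclusion.** The point holds for the parent and dentist grades. The article states that they are ordered, assigns them a test that in its ordinary form ignores order, and names a suitable rank test in the same sentence for other outcomes. If the ordinary 2×6 test is meant, power against a consistent shift is about 55% where Mann-Whitney has about 80%. The factor of 1.63 in sample size follows from the degrees of freedom and hardly depends on the assumed grade shares. The absolute power at any given odds ratio does depend on them.

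This is a loss of efficiency and interpretability in secondary outcomes. It is not a validity error and does not touch the primary analysis. For restoration integrity the point is conditional on how the score is analysed. It is a cheap improvement worth making.

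**What to change.** Amend one sentence under Data analysis and statistical evaluation:

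- Compare the 1-to-6 parent and dentist grades with the Mann-Whitney U test already planned for the visual analogue scale, or name a linear-by-linear trend chi-square. Report a common odds ratio with confidence interval from a proportional-odds model.
- Do the same for restoration integrity only if the modified USPHS/Ryge scores are analysed on three or more ordered levels.
- Keep chi-square or Fisher's exact test for binary items.
- Tabulate the grade distribution by arm.

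The cost is one sentence and one table, with no extra data. There are two downsides. The rank test has little power for non-monotone differences, which the table is there to reveal, and the odds ratio rests on the proportional-odds assumption.

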### Missing data

We anticipate various reasons for missing data (Table 3). Sample size calculation was performed accounting for possible loss to follow-up, that is, data missing at random. To prevent data missing not at random, case report forms have been designed in a way that enables and enforces complete reporting. Moreover, regular data control procedures will be performed for the early detection of missing data. Moreover, we will account for data not missing at random due to imbalanced loss to follow-up by handling drop-outs as non-success or non-survival using the intention-to-treat principle.

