**Table 3 Tab3:** **Handling of loss to follow-up**

**Level**	**Reason**	**Consequence**
Tooth	Complication	Complications leading to tooth loss will be counted as non-survival. Teeth with complications which allow the retention of the tooth will be count as non-success. Required follow-up treatments will be recorded and survived teeth will be followed up on.
	Lesion treated by other dentist	Tooth will be counted as non-success or non-survival.
	Tooth exfoliation	The last observation will be carried forward.
Patient	Adverse or serious adverse events related to treatment or material	Counteractive measures will be taken and events documented.
		Patient and tooth will be censored and the last observation carried forward.
	The patient cannot be examined (lost to follow-up)	Patient and survived tooth or teeth will be censored and the last observation carried forward.
	The patient decides to withdraw from the study.	Patient and tooth will be censored and the last observation carried forward.
Study	One to four patient(s) show adverse events related to treatment or material	Counteractive measures will be taken and events documented.
		Patient and tooth will be censored and the last observation carried forward. The study will be interrupted.
	More than four patients show adverse events or one patient shows a severe adverse event related to treatment or material	Counteractive measures will be taken and events documented.
		The study will be terminated. All patients and available teeth will be marked as censored and the last observation carried forward.

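### Lost and withdrawn children are counted as failures in the text but censored in Table 3, with no rule named as primary and carry-forward left undefined

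*Protocol article*

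**What the plan says.** The primary endpoint is a time-to-event outcome in all but name. Under Outcomes: "The primary outcome of the study will be success (not requiring any re-intervention". Under Data analysis and statistical evaluation: "Log rank tests will be used to compare success and survival between groups".

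The Missing data section refers to Table 3 and then makes two statements about loss:

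- For planning: "Sample size calculation was performed accounting for possible loss to follow-up, that is, data missing at random".
- For analysis: "we will account for data not missing at random due to imbalanced loss to follow-up", and the means given is "handling drop-outs as non-success or non-survival using the intention-to-treat principle".

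Table 3, which covers the handling of loss to follow-up, gives a different rule. For a child who cannot be examined: "Patient and survived tooth or teeth will be censored and the last observation carried forward". For a child who withdraws, and for a child with an adverse event related to treatment or material: "Patient and tooth will be censored and the last observation carried forward".

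The article does not rank these rules, does not call the failure rule a sensitivity analysis, and does not say what degree of imbalance would bring it into play.

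**The concern.** The text and the table describe the same children and give them opposite status in the same test. Under the failure rule a lost child adds an event. Under censoring the child leaves the risk set at the last examination without one. Carry-forward is a further uncertainty: read literally, it keeps the tooth as a success to month 36, which is neither of the other two.

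The planned drop-out is large, so the choice matters. The failure rule is offered as the remedy for imbalanced loss, yet it turns any difference in loss between arms directly into a difference in the primary outcome. Such a difference is plausible: children and parents know the allocation from month 6, and only one arm then has a second excavation.

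**Working it through.** **Inputs from the protocol article:** 20% annual drop-out; 66 per group before and 114 after the drop-out allowance; 300 children, taken as 150 per arm; three years of follow-up; α = 0.05, taken as two-sided. **Assumed, because the article gives no figure:** annual failure of 10% (range 5% to 20%), constant hazards, and the loss rates by arm.

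**1. How much loss the plan allows for.** The step from 66 to 114 is reproduced by 66 × 1.2³ = 114.05. It implies a loss of 1 − 66/114 = 42%. Compounding 20% a year over three years gives 1 − 0.8³ = 48.8%.

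**2. Drop-outs against true failures.** The hazards are λ_f = −ln 0.90 = 0.1054 for failure and λ_c = −ln 0.80 = 0.2231 for loss. By three years the share of children with either is 1 − (0.9 × 0.8)³ = 0.627. Of these, 0.2231/0.3285 = 68% are drop-outs. With 150 per arm that is about 64 drop-outs and 30 failures. The drop-out share is 81% at 5% annual failure and 50% at 20%.

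**3. Three-year success from the same data.**

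| Rule | Formula | Success |
|---|---|---|
| Censored | 0.9³ | 73% |
| Drop-out counted as failure | (0.9 × 0.8)³ | 37% |
| Carried to month 36 (literal reading only) | 1 − (0.1054/0.3285) × 0.627 | 80% |

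**4. Equal loss, failure rule.** A true hazard ratio of 1.3 becomes (1.3 × 0.1054 + 0.2231)/0.3285 = 1.10. This is dilution, not a false positive.

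**5. Unequal loss, failure rule, no true difference.** Take 20% versus 25% loss a year; the second loss hazard is −ln 0.75 = 0.2877.

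- Apparent hazard ratio: (0.1054 + 0.2877)/(0.1054 + 0.2231) = 1.196.
- Counted events: 150 × [1 − (0.9 × 0.8)³] + 150 × [1 − (0.9 × 0.75)³] = 94.0 + 103.9 = 198.
- Expected log-rank z: ln(1.196) × √198 / 2 = 1.26.
- Two-sided rejection: about 24%. Simulations with yearly examinations gave 23% to 26%.
- Range: 29% at 5% annual failure and 17.5% at 20%.
- Allocation is revealed at month 6, so loss can depend on arm for only about 2.5 years. Over 2.5 years there are about 178 counted events, z is 1.20 and rejection is about 22%.

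Censoring stayed near 5% in these simulations, in which loss was unrelated to outcome.

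**6. Loss that depends on outcome.** Now let random loss be 20% a year in both arms, with no true difference, and let a share of the failing children in one arm leave before the failure is recorded. If that share is 20%, 30% or 50%, censoring rejects about 12–13%, 24–25% and 60–62% of the time. The failure rule stays near 5%. These shares are assumptions too.

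**The case against.** **The failure rule may be a worst-case layer over Table 3.** The text ties it to imbalanced loss that is not at random, so it could be meant as a sensitivity analysis. The article neither says so nor sets a trigger, and choosing the rule after seeing the imbalance would be data-dependent. On this reading the dilution in step 4 falls outside the rule's intended use. It is therefore not the main argument.

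**Censoring is not the demonstrated answer.** A reader might infer from step 5 that censoring is right and the failure rule wrong. The documents do not support that. Step 5 assumes loss unrelated to outcome; step 6 shows censoring failing under the kind of loss that the text worries about. Each rule breaks under a different mechanism, so the choice of primary rule is a judgement. This objection stands.

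**Three incompatible rules would be too strong.** A reader might count failure, censoring and carry-forward as three rivals. Table 3 puts the last two in one sentence, which can mean status as at the last visit, or can concern outcomes that are not time-to-event. Against that, Table 3 uses carry-forward without censoring for exfoliated teeth, which suggests a separate rule. The firm conflict is failure against censoring, with carry-forward undefined.

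**Adverse events are a minor matter.** A reader might infer that censoring children with treatment-related adverse events biases the comparison materially. By Table 3 the study ends once more than four children have such events, or one has a severe event, so few could be censored this way before that. The first excavation is also common to both arms and precedes allocation. What remains is an inconsistency with the appeal to intention to treat.

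**A condensed article may leave details to a fuller document.** Here the rule has not been left out; the article states two that conflict.

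**Conclusion.** The contradiction is certain and bears on the primary outcome: the same children are events in the text and censored in Table 3, with no ranking and no trigger. Intention to treat does not settle it, because it fixes the arm in which a child is analysed, not whether an unobserved tooth failed.

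The size is conditional. Drop-outs match or outnumber true failures for annual failure up to 20% at the stated drop-out rate. The gap between 73% and 37% success rests on an assumed 10% annual failure. The inflated error rate of about 24% (17% to 29%) also needs unequal loss, here 20% versus 25% a year. The conflict needs settling before outcome data are seen, because the primary estimate and its error rate depend on which sentence the analyst follows.

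**What to change.** - State one primary rule for lost and withdrawn children, in the same words in the Missing data text and in Table 3. Censoring at the last attended examination fits the planned log-rank test and the missing-at-random assumption used for the sample size.
- Label drop-out as failure as a sensitivity analysis, and report the number and timing of losses by arm.
- Say which outcomes, if any, use carry-forward, and remove it from the time-to-event analysis.
- As a minor point, and for analysis only, reconcile the censoring of children with treatment-related adverse events with the intention-to-treat statement: data that are collected should be analysed in the allocated arm.

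The cost is a few reworded lines and one added sensitivity analysis. The downside is that the primary analysis then assumes non-informative loss, which the sensitivity analysis probes but cannot verify.
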